## Abstract

**Background::**

Globally, poor nutrition is a driver of many chronic diseases and is responsible for more deaths than any other risk factor. Accordingly, there is growing interest in the direct provision of healthy foods to patients to tackle diet-linked chronic diseases and mortality.

**Aim::**

To assess the effect of two healthy food interventions in conjunction with nutrition counseling and education on select chronic disease markers, food insecurity, diet quality, depression, and on self-efficacy for healthy eating, healthy weight, and chronic disease management.

**Methods::**

This parallel-arm quasi-randomized control trial will be conducted between January 2022 and December 2023. Seventy adult patients recruited from a single academic medical center will be randomly assigned to receive either: i) daily ready-made frozen healthy meals or ii) a weekly produce box and recipes for 15 weeks. Participants will, additionally, take part in one individual nutrition therapy session and watch videos on healthy eating, weight loss, type 2 diabetes, and hypertension. Data on weight, height, glycated hemoglobin, blood pressure, and diabetes and blood pressure medications will be collected in-person at the baseline visit and at 16 weeks from baseline and via medical chart review at six months and 12 months from enrollment. The primary outcome of the study is weight loss at 16 weeks from baseline. Pre- and post-intervention survey data will be analyzed for changes in food insecurity, diet quality, depression, as well as self-efficacy for health eating, healthy weight, and chronic disease management. Through retrospective chart review, patients who received standard of care will be matched to intervention group participants as controls based on body mass index, type 2 diabetes, and/or hypertension.

**Findings::**

By elucidating the healthy food intervention with better health outcomes, this study aims to offer evidence that can guide providers in their recommendations for healthy eating options to patients.

## Introduction

Globally, poor nutrition is responsible for more deaths than any other risk factor, an outcome attributable to excess daily consumption of unhealthy foods and suboptimal consumption of nearly all healthy foods and nutrients (GBD 2017 Diet Collaborators, 2019). Consumption of a healthy diet, thus, remains the cornerstone for reducing diet-linked leading causes of mortality such as heart disease, hypertension, type 2 diabetes, and obesity (Joint WHO/FAO Expert Consultation, 2003; World Health Organization, 2013; Micha et al., 2017; GBD 2017 Diet Collaborators, 2019). A healthy diet consists of diverse macro- and micronutrients as well as water consumed in appropriate proportions to meet a person’s physiological needs. Such a diet consists of wholegrains, a variety of fresh or frozen (without additives) vegetables and fruits, nuts, herbs, beans and legumes, fish and lean animal protein such as chicken, and unsaturated fats, all with little-to-no added sodium or sugar (World Health Organization, 2018; Cena and Calder, 2020).

The cardiometabolic benefits of a healthy diet are welldocumented. Dietary fiber such as that found in vegetables, fruits, nuts, and wholegrains promotes satiety, has a positive effect on cholesterol levels and glycemic control, and is known to lower the risk of heart disease, stroke and death from all causes (Cena and Calder, 2020). Vegetables, fruits, nuts, and wholegrains also contain phytochemicals, which are important bioactive compounds that modulate cellular processes such as oxidative stress, nuclear transcription, fat metabolism, and inflammation (Liu, 2013). Phytochemicals have been associated with a reduced risk of chronic diseases (Vasmehjani *et al.*, 2021; Borgonovi *et al.*, 2022). Essential amino acids, which are important for maintaining a lean body mass, are derived from animal and plant protein sources. While some animal-based proteins contain saturated fats which might contribute to cardiometabolic diseases (Cena and Calder, 2020), animal-derived amino acids are generally considered to have health benefits (Jennings *et al.*, 2015; Lonnie *et al.*, 2018), with plant protein shown to confer greater and more pervasive protection against diet-linked chronic diseases (Luo *et al.*, 2014; Jennings *et al.*, 2015; Jennings *et al.*, 2015; Malik *et al.*, 2016; Shang *et al.*, 2017; Ahnen *et al.*, 2019). Unsaturated fats, including the polyunsaturated essential fatty acids, omega-3 and omega-6, promote normal growth and reproduction and are known to have cardiovascular, neurological, and anti-inflammatory benefits as well as to prevent or improve sarcopenia and insulin resistance (Luo *et al.*, 2014; Ding *et al.*, 2017; Manuelli *et al.*, 2017; Stella *et al.*, 2018; Zhang *et al.*, 2019). Seafood, particularly oily fish, nuts, and seeds are the main sources of omega-3 fatty acids.

The preponderance of evidence supporting the health benefits of proper nutrition has led to the espousal of a food is/as medicine paradigm in health care and beyond (Mozaffarian *et al.*, 2019; Tufts University Friedman School of Nutrition Science and Policy, 2023). In the United States, clinicians are increasingly at the forefront of food is/as medicine efforts (Veldheer *et al.*, 2020), and in recent years, such endeavors have taken the form of direct provision of healthy foods to patients. Providing healthy foods directly to patients offers many benefits, including imparting practical knowledge about nutritious food items, introducing or incentivizing healthy eating, and addressing barriers such as financial and neighborhood access to healthy foods (Downer *et al.*, 2020). Direct interventions include free or subsidized medically tailored meals, medically tailored groceries, and fresh produce referral or prescription programs. Medically tailored meals are fully prepared meals designed by a professional nutritionist following individualized assessment of the recipient. Medically tailored meals are often paired with nutrition counseling and are typically targeted toward medically and socially complex individuals such as those with cancer, HIV/AIDS or heart failure, or those unable to purchase or prepare meals (Downer *et al.*, 2020). Medically tailored groceries and produce prescription/referral programs, on the other hand, are similar in that they primarily target food-insecure individuals with, or are at risk for, diet-linked chronic conditions who are able to cook and prepare meals at home. In the former intervention, grocery items are selected by a nutritionist as part of the recipient’s treatment plan, while the latter intervention offers currency, for example, vouchers or debit cards, or connection to a vendor where produce can be redeemed for free or at a discount (Downer *et al.*, 2020).

## Background

In 2019, our hospital, a nonprofit urban academic center in the Midwest United States, conducted a Community Health Needs Assessment (CHNA) through which it identified the prevention and management of chronic diseases as a significant need in the communities it serves (Cleveland Clinic Akron General, 2019). In the tri-county area served by the hospital, cardiometabolic diseases were noted to be highly prevalent, and heart disease and hypertension were documented as leading causes of mortality. The CHNA, additionally, reported that the proportion of adults with obesity in its service area was above the national average. In Summit County, the hospital’s main catchment area, adult obesity rose from 25% to nearly 30% between 2015 and 2018, with poor nutrition cited as a driver of obesity and other chronic diseases. Barriers to healthy eating identified by community members were lack of time to make meals, lack of knowledge about preparing nutritious meals, and residing in a food desert (Cleveland Clinic Akron General, 2019).

Research has shown that direct provision of healthy foods to patients aids weight loss (Cavanagh *et al.*, 2017), improves glycated hemoglobin (hbA1c) (Berkowitz, Delahanty, *et al.*, 2019), alleviates food insecurity (Berkowitz, Delahanty, *et al.*, 2019), and reduces acute health care visits (Berkowitz *et al.*, 2018; Berkowitz, Terranova, *et al.*, 2019; Berkowitz, O’Neill, *et al.*, 2019). While past research has tested direct provision of healthy meals and fresh produce with different populations, to our knowledge, no study has compared these two interventions in a parallel-arm design (Nair, 2019) with research participants drawn from the same population. Our study seeks to compare these two interventions within the same patient population to help illuminate the more efficacious healthy food intervention in improving obesity, type 2 diabetes, and hypertension, compared to standard of care. Participants in the intervention arms will also take part in nutrition counseling and education through the nutrition center of a local university. The inclusion of nutrition counseling and education in our study aims to address information gaps, with the goal of improving participants’ self-efficacy for healthy eating and chronic disease management beyond the tenure of the study. The nutrition education component is based in social cognitive theory, which postulates that change in health behavior hinges upon increase in self-efficacy to perform the desired behavior (Bandura, 2004).

Our study will collaborate with two local organizations which will supply healthy foods to participants. The first organization, SimplyEZ, is a 25-year-old meal delivery company that provides healthy ready-to-heat-and serve meals, including low-sodium and diabetic-friendly options, designed by a dietitian to customers in the Midwestern United States. The second organization, Perfectly Imperfect Produce, has the primary mission of reducing food waste and improving healthy food access for all. The organization rescues and sells aesthetically imperfect but perfectly fresh produce rejected by grocers and, additionally, operates a website featuring recipes, produce preparation, and produce storage tips accessible to the public at no cost. Our study seeks to compare these two healthy food options – ready-made healthy meals and a produce box – within the same patient population to help illuminate the more efficacious healthy food intervention in improving obesity, type 2 diabetes, and hypertension, compared to standard of care.

## Methodology

### Study aims

The primary aim of this study is to compare absolute weight change among participants receiving daily healthy meals or produce box versus matched controls (standard of care) at 16 weeks from baseline:This aim tests the hypothesis that receiving daily healthy meals will result in greater absolute weight loss compared to receiving a produce box or standard of care at 16 weeks from baseline.This aim tests the hypothesis that receiving either daily healthy meals or a produce box will result in greater absolute weight loss compared to standard of care at 16 weeks from baseline.
The secondary aim of this study is exploratory and will compare daily healthy meals or produce box versus matched controls in improving chronic disease markers:This aim tests the hypothesis that receiving daily healthy meals will result in greater improvement in hbA1c and blood pressure compared to receiving a produce box or standard of care box at 16 weeks, six months, and 12 months from baseline.This aim tests the hypothesis that receiving either daily healthy meals or a produce box will result in greater improvement in weight, hbA1c and blood pressure compared to standard of care at 16 weeks, six months, and 12 months from baseline.
To assess whether receiving daily healthy meals or a produce box in conjunction with nutrition counseling and education results in improvement in food insecurity, diet quality, depression, self-efficacy for healthy eating and healthy weight, and self-efficacy for chronic disease management from baseline to 16 weeks.

### Study design

This study is a parallel-arm quasi-randomized control trial with nonequivalent matched controls, which will be conducted between January 2022 and December 2023. Seventy adult patients recruited from our ambulatory practice will be randomly assigned to receive either: i) daily healthy frozen meals or ii) a weekly produce box and recipes for 15 weeks. Each study arm will comprise 35 patients with a documented diagnosis of obesity (body mass index [BMI] equal to or greater than 30kg/m^2^) and one or more of the following conditions: pre-type 2 diabetes/type 2 diabetes or hypertension. Participants will complete an in-person baseline visit and a follow-up visit at 16 weeks from baseline, and their medical charts will be reviewed for trends in these biomarkers at six months and 12 months from baseline. Healthy meals or a produce box will be shipped to the home address of participants once a week. Healthy meals provided in the study are low-sodium and diabetic-friendly ready-to-heat and serve breakfast, lunch, and dinner items. The produce box provided in the study will comprise fresh vegetables and fruits. For participants receiving a produce box, recipes utilizing items contained in the box will be available at the vendor’s website.

All participants will complete one individual medical nutrition therapy session via phone with a dietitian. The individual medical nutrition therapy appointment will occur within two weeks of enrollment in the study. A total of four nutrition and health videos, each under 10 minutes in length, will be available for participants to view between weeks 3 and 15 of the study. The complete study procedures are outlined in Table 1. Participants will be required to view the videos on healthy eating and weight loss and, as applicable to their health status, videos on type 2 diabetes and hypertension (see Table 2). The Healthie application (https://www.gethealthie.com/?afmc=a46i) will be utilized for nutrition education programming. Through the Healthie application, participants will receive automated text and/or email reminders to view educational videos. This feature is designed to drive compliance and completion of the nutrition education component. A report will be generated to provide completion percentage and other details based on participant engagement. The Healthie application is compliant with the US Health Insurance Portability and Accountability Act.

**Table 1. tbl1:** Schedule of study activities

Study activity	Baseline visit (W0)	Week 2 (W0–W2)	Week 3 – 15 (W3–W15)	Week 16 visit (W16 ± 7 days)	6 months	12 months
Informed consent process	x					
Anthropometric data (weight, height, and blood pressure)	x			x	x	x
HbA1c	x			x	x	x
Completion of study questionnaires	x			x		
Individual nutrition counseling session		x				
Nutrition education videos			x			

**Table 2. tbl2:** Expected viewership of nutrition education videos

	Video title			
	Introduction to nutrition	Nutrition and weight loss	Nutrition and diabetes	Nutrition and hypertension
All participants	x	x		
Participants with pre-/type 2 diabetes			x	
Participants with hypertension				x
Participants with pre-/type 2 diabetes AND hypertension			x	

The control group will comprise 70 participants matched to intervention group participants based on BMI, diagnosis of pre-type 2 diabetes/type 2 diabetes, and/or hypertension. Control group participants will be identified from the electronic medical record, Epic^®^, after enrollment of all intervention arm participants has been completed. A flow chart of participant recruitment and completion of study activities is shown in Figure 1. Our study protocol adheres to the SPIRIT guidelines for clinical trial protocols (Chan *et al.*, 2013) and is registered on ClinicalTrials.gov with identifier NCT05174078.

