## Data collection

### Demographic and clinical data

Participants’ date of birth, sex, race, and ethnicity will be collected as part of demographic data. Objective health data that will be collected are weight, height, hbA1c, blood pressure, prediabetes/diabetes diagnosis and classification, hypertension diagnosis and classification, diabetes and blood pressure medications, and comorbid chronic conditions. These data will be collected in-person at the baseline visit and at 16 weeks from baseline and via chart review of routine care at six and 12 months from enrollment in the study.

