### Data analysis

The independent variables in this study are study arm (healthy meals, produce box, and matched controls [standard of care]), nutrition counseling and education, and time (pre-intervention, 16 weeks, six months and 12 months). The primary dependent variable (outcome) is absolute weight change at 16 weeks between groups. The secondary dependent variables (outcomes) are as follows: i) absolute weight change at six months and 12 months from baseline; ii) change in hbA1c, dosage, and number of diabetes medications; iii) change in dosage and number of blood pressure medications, and; iv) change in numeric rating from baseline to 16 weeks for food insecurity, diet quality, depression as well as self-efficacy for health eating, healthy weight, and chronic disease management. A final outcome of interest is satisfaction rating for the interventions provided in the study, measured using a non-validated questionnaire developed for this study.

Descriptive statistics will be calculated for demographic data and for each dependent variable by group, nutrition counseling and education, and time. Separate repeated-measures ANOVAs will be conducted for each dependent variable with the between subjects factor group (healthy meals, produce box, and matched controls) and the within subjects factor time (pre-intervention and 16 weeks). *Post hoc* testing will be conducted as appropriate. Effect sizes will be calculated between pre-intervention and 16 weeks to capture the changes from pre- to post-intervention. Missing data will be analyzed using an intention-to-treat strategy. Statistical analysis will be performed by a biostatistician using SAS statistical software. The biostatistician will be blinded to the intervention for each group to eliminate potential bias during data analysis.

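### HbA1c and drug outcomes are averaged over participants who need not have the condition, so the exploratory disease-marker results do not match the stated question

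*Protocol article*

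**What the plan says.** Eligibility (Protocol article, Study design) is obesity "and one or more of the following conditions: pre-type 2 diabetes/type 2 diabetes or hypertension". Both conditions are not required.

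Under the second aim, the Study aims section predicts: "receiving daily healthy meals will result in greater improvement in hbA1c and blood pressure compared to receiving a produce box or standard of care". The same section qualifies it: "The secondary aim of this study is exploratory". The Background section frames the purpose as finding which food option does more for obesity, type 2 diabetes and hypertension.

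The Data analysis section lists among the secondary outcomes "ii) change in hbA1c, dosage, and number of diabetes medications; iii) change in dosage and number of blood pressure medications". Blood pressure itself is in the hypothesis but not in this list. The analysis rule is: "Separate repeated-measures ANOVAs will be conducted for each dependent variable with the between subjects factor group". The group factor has three levels (meals, produce, matched controls) and the time factor has two (pre-intervention and 16 weeks). No outcome is limited to participants with a given diagnosis. The only wording near an analysis set is "Missing data will be analyzed using an intention-to-treat strategy".

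Table 1 schedules HbA1c without limit by diagnosis. Diagnoses of (pre)diabetes and hypertension are collected (Demographic and clinical data) and are used to match the controls (Study design). Only the education videos are tailored to diagnosis (Table 2).

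**The concern.** The aim asks about improvement in markers of two diseases, but the analysed groups contain people who may not have the disease in question. Someone enrolled on hypertension alone usually has no diabetes drugs to reduce and less room for HbA1c to fall. Someone enrolled on (pre)diabetes alone is in the same position for blood pressure and its drugs. An average over both kinds of participant understates the effect in those with the disease, by an amount that depends on the case mix, which the plan neither fixes nor predicts.

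A second problem concerns the controls. They are found by retrospective chart review, whereas intervention participants have HbA1c measured in person at baseline and 16 weeks. A control with hypertension only may have no HbA1c on file, while an intervention participant with hypertension only will have one. The people who contribute HbA1c may then differ in case mix between groups even though the groups were matched on diagnosis.

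**Working it through.** **The plan's own figure.** The only sample-size calculation is for weight. With means 92, 78.4 and 85.2 kg and SD 16, the squared deviations from the mean of 85.2 sum to 6.8² + 6.8² = 92.48. At 28 per group the noncentrality is 28 × 92.48 / 256 = 10.1. Power is 0.789 at 27 and 0.805 at 28 per group, so 28 is reproduced. It says nothing about HbA1c, blood pressure or drugs.

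**Inputs for this point.** The plan gives 35 per intervention arm. It does not give the share p without the condition, the standardized effect d in those with it, or the ratio r of the SD of change in unaffected to affected participants. These are assumed over a range, with zero effect in the unaffected.

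**Dilution of the mean.** All-participant effect = (1 − p) × d.
- p = 0.2: 80% of d
- p = 0.4: 60%
- p = 0.5: 50%

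**Signal-to-noise, restricted against all.** With the SD in the affected set to 1:
- all participants: z = (1 − p)d / √(2[(1 − p) + p r²]/n)
- restricted: z = d / √(2/[(1 − p)n])
- ratio = √[(1 − p) + p r²] / √(1 − p)

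| p | r = 1 | r = 0.3 | r = 0 |
|---|---|---|---|
| 0.2 | 1.12 | 1.01 | 1.00 |
| 0.4 | 1.29 | 1.03 | 1.00 |
| 0.5 | 1.41 | 1.04 | 1.00 |

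r = 1 might suit blood pressure, r = 0.3 HbA1c, and r near 0 drug counts. None of these values is in the documents.

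**Refinement.** The ratio omits the extra variance p(1 − p)d² that arises in the treated arm when only some participants respond. A two-arm normal approximation that includes it, with 35 per arm, two-sided alpha 0.05 and assumed d = 0.8, gives power for all participants against condition-only:
- r = 1: 0.74 against 0.85 (p = 0.2); 0.49 against 0.74 (p = 0.4); 0.36 against 0.66 (p = 0.5)
- r = 0.3: 0.82 against 0.85; 0.66 against 0.74; 0.56 against 0.66

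These gaps depend on a large assumed effect. With d = 0.5 and r = 0.3 they are 0.45 against 0.46 at p = 0.2 and 0.28 against 0.32 at p = 0.5.

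**Remaining size.** Restricting leaves 35 × (1 − p) per arm: 28, 21 or about 17.

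**Chance difference between the randomized arms.** The 95% range for the difference in p is ±1.96√(2p(1 − p)/35): ±0.19 at p = 0.2 and ±0.23 at p = 0.5.

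**Case mix against controls.** Matching makes the enrolled share p similar across groups. The HbA1c analysis uses those with values. In the limit where no unaffected control has HbA1c on file, the unaffected share is p in the intervention arms and 0 among the analysed controls. The true position is unknown and lies between that and full balance.

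**The case against.** The strongest reply is that the article never says these outcomes are analysed in everyone. It names no analysis population, and a fuller plan might restrict them. That is fair as far as it goes, but the article does state one rule for every dependent variable with whole groups as the factor, so a later restriction would change a published rule.

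It can also be said that the average over all enrolled participants is a legitimate quantity for an aim worded around chronic disease markers. It is, but it does not answer the question in the Background section, which is about improving type 2 diabetes and hypertension.

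Several stronger readings are tempting and are not supported:
- **That unaffected participants cannot improve, or have HbA1c below the prediabetes range.** No HbA1c threshold is given, and absence of a diagnosis is not a laboratory value. HbA1c and blood pressure may fall with weight loss. Less room is the defensible claim; only for drug counts is it usually none.
- **That restriction brings a large gain in power generally.** The 12–41% gain needs equal SDs. For the outcomes in the Data analysis list it may be slight or nil.
- **That the lack of stated stratification by diagnosis biases meals against produce.** A chance imbalance of about 19 to 23 percentage points is possible, but it is noise and not systematic bias.
- **That a shifting case mix at six and 12 months distorts the planned test.** Those values come "via chart review of routine care at six and 12 months from enrollment in the study", but the ANOVA uses only pre-intervention and 16 weeks, and the Strengths and limitations section already concedes that missing data will hinder the later time points.

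Finally, the aim is exploratory and the primary weight outcome is unaffected. Both points stand and limit the weight of the finding.

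**Conclusion.** The point holds in a limited form. Eligibility on either condition, combined with one ANOVA per outcome over whole groups, gives exploratory HbA1c and drug results, and a test of the blood pressure hypothesis, that average over people with little or, for drug counts, usually nothing to improve. Under zero effect in the unaffected, the estimate is 50–80% of the effect in those affected for p between 0.5 and 0.2. Both the zero effect and p are assumptions. The main loss is interpretability, since the estimate does not match the question. Loss of signal-to-noise is secondary, from about nil to 41% depending on SDs that the documents do not give. A case-mix difference between controls and intervention participants in the HbA1c analysis is plausible but cannot be sized. The conclusion on weight is not affected.

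**What to change.** In Study aims and Data analysis, name the main analysis set by outcome:
- HbA1c and diabetes drugs: participants with (pre)diabetes at baseline, with their matched controls.
- Blood pressure and blood pressure drugs: participants with hypertension at baseline, with their matched controls. Add blood pressure to the outcome list, so that the list agrees with the hypothesis.
- Weight: everyone, as now.

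Keep the all-participant result for the disease markers as a secondary display, and report the number with each diagnosis and the number with usable HbA1c by group.

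This changes wording only: the diagnoses are already collected and matched on, and no new data are needed. The cost is a smaller n for these exploratory outcomes, about 17 to 28 per arm for p between 0.5 and 0.2. Restricting to (pre)diabetes should also limit the case-mix problem, because controls with that diagnosis have a clinical reason to be tested.

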### Study population

Current patients at our ambulatory practice who are 18 years and older, and are of any gender and race, are eligible for enrollment in the study. Patients who have food allergies, are pregnant or planning to become pregnant, have no access to internet, or require English language interpretation will be excluded from participation. Additional exclusion criteria are participation in nutrition counseling with our partnering organization within the past six months, current participation in a structured weight loss program, or current use of weight loss medications. Medications prescribed for other conditions but that may have a weight loss effect, for example, metformin or GLP-1 agonists prescribed for diabetes treatment or topiramate prescribed for migraine headaches, will not result in the exclusion of potential participants.

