One limitation of this study is the relatively small sample size of 70 participants who will receive interventions. Consequently, participant attrition from the study will threaten the study power. A second limitation of the study is the lack of a parallel control group. Study controls will consist of 70 matched participants identified via the electronic health record from the same patient population as the intervention arm participants. Due to funding and ethical reasons, this study is unable to utilize a true control group for comparison with the intervention groups. Our study population faces many social challenges, including food insecurity; thus, it is important to ensure that would-be controls receive compensation comparable to the healthy food items received by intervention arm participants. The small amount of the study grant limits the ability to compensate or offer equivalent healthy food items to controls after the intervention period. A third limitation of this study is the relatively short timeline (16 weeks) in which the primary outcome will be assessed. Because this study will offer interventions for only 15 weeks, and to guard against the high attrition common in studies with a lengthy period of follow-up, assessing the primary outcome soon after completion of the interventions is deemed appropriate. With the expected weight loss of one to two pounds a week over the 15-week intervention period, the timeline for the primary outcome is still clinically meaningful. Additionally, biomarkers of interest will be collected via review of the electronic medical record at six months and 12 months from baseline. While these data will allow for the assessment of study outcomes longitudinally, a significant amount of missing data will hinder such a pursuit. A final limitation of the study is the lack of blinding to treatment arm assignment among assessors collecting self-reported data. To mitigate this limitation, during the baseline visit, self-reported data will be collected prior to random allocation to intervention arms. In addition, the biostatistician analyzing the data will be blinded to the treatment arms. Despite the aforementioned limitations, we anticipate that the results of this study will add to the growing body of scholarship on the impact of direct healthy food interventions on chronic diseases.

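### The rule for selecting chart controls does not apply the enrollment exclusions to them, so patients ineligible for a food arm can enter the primary weight comparison as standard of care

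*Protocol article*

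**What the plan says.** **Controls.** The Study design section says "The control group will comprise 70 participants matched to intervention group participants based on BMI, diagnosis of pre-type 2 diabetes/type 2 diabetes, and/or hypertension". The Abstract gives nearly the same list: patients who received standard of care will be "matched to intervention group participants as controls based on body mass index, type 2 diabetes, and/or hypertension". On source and timing, Study design says "Control group participants will be identified from the electronic medical record, Epic^®^, after enrollment of all intervention arm participants has been completed". Strengths and limitations adds that controls are "identified via the electronic health record from the same patient population as the intervention arm participants". The text says nothing more about who may be a control.

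**Food arms.** The Study population section describes adult patients of the practice who "are eligible for enrollment in the study". It then lists the exclusions: "Patients who have food allergies, are pregnant or planning to become pregnant, have no access to internet, or require English language interpretation will be excluded". Further exclusions are counseling with the partnering organization in the previous six months, "current participation in a structured weight loss program, or current use of weight loss medications". Drugs given for another condition that happen to affect weight (its examples are metformin, GLP-1 agonists for diabetes and topiramate for migraine) do not exclude.

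**Where the controls are used.** Both primary hypotheses under Study aims include a comparison with standard of care on absolute weight change at 16 weeks. The sample size section assumes that control weight does not change.

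**The concern.** The two sides of the primary comparison appear to be drawn under different entry rules. Several exclusions protect the weight endpoint: they keep out people who are already losing weight by other means, or whose weight will change because of pregnancy. The control rule mentions none of them. A record search on BMI and diagnosis in the same practice can therefore return patients on weight loss drugs, in weight loss programs, recently counseled by the partnering organization, or pregnant.

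This differs from ordinary confounding by unmatched covariates. A feature barred from the food arms has no counterpart there, so covariate adjustment would rest on extrapolation. Restricting the control pool is the direct remedy. At stake is every contrast with standard of care. The randomized contrast of meals with produce is not affected.

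**Working it through.** **1. The two entry rules side by side**

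| Criterion | Food arms (Study population, Study design) | Chart controls (Abstract, Study design, Strengths and limitations) |
|---|---|---|
| BMI; pre-/type 2 diabetes and/or hypertension | Required | Matching factors |
| Same practice population | Yes | Yes |
| Age 18 or over | Required | Not stated |
| Pregnant or planning pregnancy | Excluded | Not stated |
| Current weight loss medication | Excluded | Not stated |
| Current structured weight loss program | Excluded | Not stated |
| Partner counseling in past six months | Excluded | Not stated |
| Food allergy, no internet, interpreter need | Excluded | Not stated |
| Metformin, GLP-1 agonist for diabetes, topiramate for migraine | Allowed | Not stated |

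Rows four to seven bear directly on weight. The food allergy, internet and interpreter criteria mainly concern delivery of the intervention. The drugs in the last row are allowed in the food arms, so a control taking one creates no asymmetry.

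**2. The plan's own figure**

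Inputs from Sample size determination: means 92, 78.4 and 85.2 kg, SD 16, alpha 0.05, power 0.80.

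- Planned effects: 92 − 78.4 = 13.6 kg (meals) and 92 − 85.2 = 6.8 kg (produce). These match 30 lb and 15 lb.
- Grand mean: (92 + 78.4 + 85.2)/3 = 85.2.
- Noncentrality: n × Σ(mean − grand mean)²/SD² = 28 × (6.8² + 6.8² + 0)/256 = 10.1.
- Power from the noncentral F distribution: 0.789 at 27 per group and 0.805 at 28.

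The stated 28 per group is reproduced, and applying exclusions to controls does not change it.

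**3. Shift in the control mean**

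Assumptions, not in the document: a fraction f of the 70 controls would have been ineligible for a food arm, and their weight changes by d kg over 16 weeks. Shift = f × d.

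- Low: 0.05 × 4 = 0.2 kg (f is 3.5, or about 4, of 70).
- High: 0.20 × 8 = 1.6 kg (f is 14 of 70).
- Against produce: 0.2/6.8 = 2.9%; 1.6/6.8 = 23.5%.
- Against meals: 0.2/13.6 = 1.5%; 1.6/13.6 = 11.8%.

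**4. What a downward shift does to the planned test**

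The control mean is lowered, with everything else as planned and 28 per group:

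| Shift (kg) | Produce minus control, size (kg) | Omnibus power |
|---|---|---|
| 0 | 6.8 | 80.5% |
| 0.5 | 6.3 | 77.3% |
| 1.0 | 5.8 | 73.9% |
| 1.6 | 5.2 | 69.6% |

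These powers use the plan's equal-group calculation. With 28, 28 and 56 evaluable patients, reflecting the planned 70 controls, unshifted power would be 91.9%. The main harm is therefore bias in the estimate rather than lost power. Controls who gain weight, as in pregnancy, move the mean the other way and exaggerate the food effect. A mix could partly cancel.

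**The case against.** The strongest reply is that the document is silent rather than wrong. The exclusions stand under a heading about the study population as a whole, the article calls the controls participants, and it draws them from the same patient population. Matching factors are also not an eligibility list: the article says what controls are matched on and does not print the record query. A journal article condenses, the recruitment flow chart is not visible here, and the article openly labels its controls nonequivalent.

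Part of this stands. A reader might infer that the protocol positively restricts the exclusions to enrolled patients and selects controls on BMI and diagnosis alone. No sentence says either, so that reading is not supported.

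The reply does not remove the problem, for three reasons:

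- The word participants cannot carry the exclusions across. The article also uses it, without qualification, for those who complete a nutrition therapy session and watch the videos, which chart controls do not.
- A shared source population is not a filter. The exclusions are needed because such patients can occur in that practice.
- Even on the generous reading, criteria tied to the present or to the past six months cannot be applied to a retrospective control without an index date, and none is given.

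The general admission of nonequivalence does not mention different entry rules. It is fair to add that controls whose charts show an excluded feature could be dropped later in a sensitivity analysis. That is the same restriction, made at a point when outcomes may already be known.

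**Conclusion.** The concern holds in a limited form. The only stated control rule is matching on BMI and diagnosis within the same patient population, and nothing applies the enrollment exclusions to controls. Followed as written, it can admit ineligible patients to the primary weight comparison.

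The size is conditional. A shift of 0.2-1.6 kg, or about 3-24% of the planned produce effect and 1.5-12% of the planned meals effect, rests wholly on the assumed 5-20% prevalence and 4-8 kg change. Nothing in the document supports or refutes those inputs.

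Two stronger conclusions might be drawn and should not be. The first is that the bias runs in a known direction: it depends on the unknown mix of treated and pregnant controls. The second is that the shift could reach about a third of a meaningful effect. That figure comes from setting the worst case against the 5% loss mentioned in the Discussion (5% of 92 = 4.6 kg; 1.6/4.6 = 35%). The differences the trial is planned on are 6.8 and 13.6 kg, and the fractions of those are smaller.

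This should be changed because it is cheap to prevent and hard to repair afterwards. It does not by itself invalidate the trial.

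**What to change.** In the control-group paragraph of Study design, state that a control must meet the Study population criteria, in the same terms, as far as the chart shows them, at a defined control index date:

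- age 18 or over;
- not pregnant;
- no current weight loss medication and no current structured weight loss program;
- no counseling with the partnering organization in the prior six months (this exact criterion, since screening out any nutrition referral would be stricter for controls and create a new asymmetry);
- where recorded, no food allergy and no interpreter need.

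Keep the existing allowance for drugs prescribed for other conditions, so that it applies equally to both sides. Apply the filters before matching and without sight of follow-up weight. List the criteria a chart cannot show (internet access, planning pregnancy) under limitations.

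The cost is a few filters in the record query, a somewhat smaller control pool and a little more chart review. Controls are to be identified only after intervention enrollment is complete, so the rule can be set before any are selected.
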